### Purpose

The purpose of this study is to evaluate whether use of MT4C-In Care over 2 months is effective to decrease loneliness and grief, and increase hope, general self-efficacy, social support and mental health as compared to an educational control group. It will address the following research questions:
Is there a 2 month (immediately post-intervention) and 4 month (2 months post-intervention) increase in mental health, general self-efficacy, social support and hope, and decrease in grief and loneliness, in carers of a person living with dementia residing in LTC using MT4C-In CARE compared to an educational control group?Do carers of persons living with dementia residing in LTC perceive My Tools 4 Care- In Care helps them with the transitions they experience?

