### Power and sample size

We aim to recruit a convenience sample of 280 participants, 140 in each of the intervention and control groups. Our design for the outcome analysis includes three repeated measurements to observe how the change in outcomes over time differs between the intervention and control group. This sample size achieves 89% power to detect a 15% difference in the mental health summary score between the two groups over time, when alpha level is 5%. This calculation assumed a Compound Symmetry covariance structure, a proportion of 30% in group 2, and correlation between observations on the same subject of 0.50.

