#### Outcome analysis

Outcome analysis will include descriptive statistical analysis of data as well as analysis to understand the effect of MT4C-In Care on primary and secondary outcomes. To assess the impact of MT4C-In Care on the MCS, the primary outcome, we will use generalized estimating equations (GEE), and will run models using PROC GENMOD in SAS Version 9.3 [42]. The SF-12v2 MCS score is a continuous variable. Variables included in the GEE model will be group (intervention, control), time (baseline, 2 months, 4 months), and a group x time interaction term, which tests the hypothesis that MT4C-In Care promotes better mental health at 2 months and 4 months in the intervention as compared to the control group [43]. If a significant intervention effect is detected in this model, additional covariates (e.g., age, gender) will be added to adjust for statistically significant baseline differences observed in demographic characteristics between the intervention and control group. To model time, we will plot the mean MCS values in each group at each time period. Time will be included as either a continuous variable (if the plot suggests a linear trend) or a categorical variable (if the plot suggests a non-linear trend).

A key advantage of GEE, as compared to linear regression, is that no assumption is made that data are normally distributed. SAS allows the user to choose the most appropriate distribution and link function. In this study, we will select link function that is a best fit for the distribution of the participants’ MCS scores. If we observe a negative skew in MCS scores (as is the case in many populations), we will use a reflected transformation which can normalize the data [44], allowing for use of the identify link function which is used with a normal distribution.

While outcome analysis will follow the intent to treat principle, sensitivity analyses will also be completed to assess impact of the intervention upon outcomes with level of use as a covariate. The aim of the latter analysis is to explore whether amount of use of MT4C-In Care influences the impact of the intervention upon outcomes.

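### The primary test is chosen between linear and categorical time from a plot of MCS means by arm, which raises type I error modestly and can halve the reported 2-month effect; the outcome scale is also left to the data

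*Protocol article*

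**What the plan says.** In the protocol article, Outcome analysis, the primary model is a GEE for the MCS with group, time (baseline, 2 and 4 months) and their interaction. The interaction is meant to test benefit at both follow-up visits. This matches the question under Purpose: "Is there a 2 month (immediately post-intervention) and 4 month (2 months post-intervention) increase in mental health".

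The coding of time is then left open. "To model time, we will plot the mean MCS values in each group at each time period", and "Time will be included as either a continuous variable (if the plot suggests a linear trend) or a categorical variable" if the trend looks non-linear. The means are plotted by arm. There is no numeric criterion, no default coding and no blinding of the plot.

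The same section gives as an advantage of GEE that "no assumption is made that data are normally distributed". It then says the link will be the one that best fits the distribution of MCS scores and that, if the scores are negatively skewed, "we will use a reflected transformation which can normalize the data". No skewness threshold and no specific function is named. The analyses of the five secondary outcomes are to follow the same approach.

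**The concern.** Linear and categorical time give different primary tests with different targets. One is a 1-df test of a difference in slope; the other is a 2-df test of any difference in change at 2 or 4 months. When the data that will be tested also decide which test is used, the nominal 5% no longer applies to the procedure as a whole.

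The linear version also fits the question badly. With equally spaced visits its slope depends only on baseline and 4 months, so the visit immediately after the intervention does not enter the test, and the 2-month effect is an interpolation.

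The scale of the outcome is a separate matter. A reflected score reverses the direction of benefit, and a non-linear transformation or non-identity link replaces the difference in mean MCS points with another quantity. Until the data are seen, nobody can say what the primary estimate will measure.

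**Working it through.** **Inputs from the protocol (Power and sample size).** "We aim to recruit a convenience sample of 280 participants, 140 in each of the intervention and control groups"; three repeated measurements; compound symmetry with within-subject correlation 0.50; "when alpha level is 5" percent.

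**Assumptions.** Two-sided test; SD 10 MCS points (the type I results do not depend on it); complete data. The plan imputes missing values, so each analysed dataset would be complete.

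**1. The plan's own figure.** The text says "This sample size achieves 89% power to detect a 15% difference in the mental health summary score between the two groups over time". This reproduces as a comparison of proportions, 45% against 30%:
- Effective n per arm = 140 × 3 / (1 + 2 × 0.5) = 210.
- Null SE = √(2 × 0.375 × 0.625 / 210) = 0.0472; alternative SE = √((0.2475 + 0.21) / 210) = 0.0467.
- Power = Φ[(0.15 − 1.96 × 0.0472) / 0.0467] = Φ(1.23) = 0.89.

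The calculation concerns a binary outcome averaged over visits. It supports neither coding of time for a continuous MCS.

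**2. What linear time estimates.** For visits at 0, 2 and 4 months, under independence or exchangeable working correlation, the slope weights are (−1, 0, +1)/4 per month. Let D0, D2 and D4 be the between-arm differences. The implied difference in change from baseline at 2 months is 2 × (D4 − D0)/4 = (D4 − D0)/2.

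| True pattern (D0, D2, D4) | Linear model's 2-month change |
|---|---|
| (0, d, d) | 0.5d |
| (0, d, 0.5d) | 0.25d |
| (0, d, 0) | 0 |

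For (0, d, d) the fitted between-arm differences are 0.17d, 0.67d and 1.17d, so the line also puts a spurious difference at baseline.

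**3. Type I error of the plot rule.** The slope contrast (−1, 0, 1) and the curvature contrast (1, −2, 1) are uncorrelated under compound symmetry, and the 2-df statistic is Z_slope² + Z_curv². Take the stand-in rule that a plot looks non-linear when |Z_curv| > c. If curvature is judged on the between-arm difference,

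error = 0.05 × P(|Z_curv| ≤ c) + P(|Z_curv| > c and Z_slope² + Z_curv² > 5.99).

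For c = 1 this is 0.05 × 0.683 + 0.038 = 0.034 + 0.038 = 0.072. A simulation of 400,000 trials agrees, and also covers curvature judged within each arm (non-linear if either arm exceeds c):

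| c | Judged within arms | Judged on between-arm difference |
|---|---|---|
| 0.5 | 5.5% | 6.3% |
| 1.0 | 6.5% | 7.2% |
| 1.5 | 7.1% | 7.5% |
| 1.96 | 6.8% | 7.2% |

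Either coding fixed in advance gives 5.0%.

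**4. How often linear is chosen, and power.** The variance of a between-arm difference in change is 4 × 100 × (1 − 0.5) / 140 = 1.43, so SE = 1.195. A 3-point (0.3 SD) effect has z = 2.51. The 2-df noncentrality is (4/3)(z2² − z2·z4 + z4²).

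| Pattern (points) | Power, linear | Power, 2-df | Power, plot rule | Linear chosen |
|---|---|---|---|---|
| (0, 3, 3) | 71% | 74% | 74–80% | 2–70% |
| (0, 3, 0) | 5% | 74% | 74% | under 0.1% to 17% |
| (0, 1.5, 3) | 71% | 61% | 63–73% | 15–95% |

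Because slope and curvature contrasts are uncorrelated, in trials where the between-arm rule picks linear for (0, 3, 3), the 2-month change averages 1.5 points, not 3.

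**5. Scale.** In a simulation of 6,000 negatively skewed trials, choosing the scale from pooled skewness gave type I error of 5.2%, against 5.3–5.5% for each scale fixed. The Monte Carlo standard error is √(0.05 × 0.95 / 6,000) = 0.3 points, so these do not differ. Inflation (8.0%) appears only if the best p-value among raw, log and square-root scales is kept, which the plan does not propose.

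**The case against.** The plan switches to categorical time when the plot is not straight, and that protects it in the worst case. A reader might infer from step 4 that a 2-month-only effect would be lost, with power falling from 74% to 5%. That compares two fixed models. A rise followed by a return to baseline nearly always looks non-linear, and power under the rule stays at about 74%. This part of the defence stands.

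A reader might also infer that link and transformation are chosen from the plots, or that they inflate type I error. The text does not support this: the plot governs time only, the other two choices rest on the score distribution with no split by arm, and step 5 shows no inflation on pooled data.

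It is also fair that a categorical model contains both visit contrasts, that an omnibus 2-df test is standard, and that gradual build-up is compatible with the protocol's framework, in which the MCS is the distal outcome reached through mediators. A straight line is therefore not ruled out.

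None of this removes the data-driven rule. The protocol itself states it, so an analysis plan that is not shown cannot make the sentence harmless. Nor does the switch cure the sustained pattern, where linear may be picked in 2–70% of trials depending on how the plot is read.

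**Conclusion.** The point holds for the coding of time. Selecting the primary test from MCS means by arm raises type I error from 5.0% to about 5.5–7.5%, a modest amount. When linear time is picked, the 2-month visit drops out of the slope, and a sustained effect is reported at half size as a change from baseline. Power to detect a sustained effect is not lost; the harm is a wrong 2-month estimate and a test whose level is not the stated one.

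For link and transformation the defect is narrower: the effect measure is undefined, the sign may be reversed, and the result may not be in MCS points. How much a transformation would change effect size or power cannot be stated, because the protocol gives no SD, skewness or function.

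The figures rest on 140 per arm, correlation 0.5, compound symmetry, complete data, a two-sided test and cut-offs of 0.5 to 1.96 standard errors standing in for a visual judgement. The power figures also assume SD 10.

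**What to change.** State that time is categorical in all models. State that the primary model uses the untransformed MCS, the identity link and robust standard errors, whatever the skew. Keep the 2-df group x time test as primary, and report from it the between-group contrasts in change at 2 and at 4 months. The sponsor should prespecify how the two contrasts are handled for multiplicity: two unadjusted 5% tests at correlation 0.5 give 9.0%. Ranking one visit above the other would be a design decision, since the protocol pairs them.

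Plots of means remain as description, and transformed or other-link models become sensitivity analyses. Apply the same to the five secondary outcomes.

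The cost is wording, plus some power if the effect is truly linear: for 0.15 SD at 2 months and 0.30 SD at 4 months, the 2-df test has 61% against 71% for the slope test. In return the test keeps its 5% level and the 2-month effect is estimated from the 2-month data.

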## Methods/design

### Study design

This pragmatic mixed methods randomized controlled trial is longitudinal, multi-site, and involves repeated measures. Participants are randomly assigned to an intervention or control group using REDCap, a secure, password-protected web application housed by the University of Alberta. The intervention group receives an educational resource and access to MT4C-In Care over a two-month period. The educational control group also receives the educational resource but will not be granted access to MT4C-In Care until the study period is over. Recruitment and data collection are planned between February 2020 and June 2021 in four provinces (Alberta, Saskatchewan, Manitoba and Ontario). Outcome data collection will occur at baseline, and 2 and 4 months from the start of the intervention. Process data collected at 2 and 4 months include qualitative data related to participant perceptions of MT4C-In Care and quantitative data related to frequency of use. Quantitative and qualitative data related to study processes (e.g., frequency and reasons for missing data) will be collected concurrently throughout the study. The qualitative data will help to explain the quantitative findings.

Reporting of this protocol followed the SPIRIT (Standard protocol items: recommendations for interventional trials) [25] guidelines for reporting protocols (SPIRIT checklist in supplementary files). This study received ethical approval from the University of Alberta Health Research Ethics Board (#Pro00090771), University of Saskatchewan Research Ethics Board (#1385), Education/Nursing Research Ethics Board at the University of Manitoba (E2019:127), and the Hamilton Integrated Research Ethics Board (#7659). If there are any changes in the protocol an amendment will be sent to the respective ethics boards for approval.

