### Intervention: my tools 4 care-in care

The intervention group will receive via email the educational resource provided to the control group and instructions on how to access to the MT4C-In Care site immediately following baseline interviews. MT4C-In Care access will occur for 2 months via an assigned web link and unique username and password. Participants will access the MT4C-In Care tool as frequently as desired, and will choose which content to engage with. They may choose not to access MT4C-In Care at any time. Some activities prompt the participants to enter information into the site, and this information will not be accessed by anyone, including the research team. The components of MT4C-In Care include a home page which introduces the toolkit and sections: a) “About Me” (contains guided evidence-based activities), b) “Common Changes to Expect”, c) “Frequently Asked Questions”, and d) Resources. More detailed information about My Tools 4 Care-In Care is published elsewhere [24].

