#### MT4C-in care checklist

MT4C-In Care checklist will be used to collect data on access and use of MT4C-In Care. Data will be collected at 2 months following the start of the intervention. Participants in the intervention group will be asked to complete the MT4C-In Care self-report checklist during the interview. The questions include: 1) how often they use MT4C-In Care, b) the total time spent on MT4C-In Care and c) content accessed over the past 2 months. They will also be asked three dichotomous questions about whether MT4C-In Care improved their knowledge and skills, mental health, and well-being, from their perspective. As well data will be collected on the utilization of other caregiver support websites and support groups. There will be no prohibited interventions during this study. A copy of the checklist can be found in the supplementary files.

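### The planned adjustment for level of use cannot show whether amount of use changes the intervention's effect, because use is self-selected after randomisation and exists in one arm only

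*Protocol article*

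**What the plan says.** All references are to the protocol article.

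- **Outcome analysis.** The main model for MCS is a GEE with group, time and group x time, analysed by intent to treat. The same sentence adds that "sensitivity analyses will also be completed to assess impact of the intervention upon outcomes with level of use as a covariate". The stated aim is "to explore whether amount of use of MT4C-In Care influences the impact of the intervention upon outcomes".
- **MT4C-in care checklist.** Use is measured by self-report: "Participants in the intervention group will be asked to complete the MT4C-In Care self-report checklist during the interview". On timing: "Data will be collected at 2 months following the start of the intervention". The Study design section places frequency-of-use data at 2 and 4 months. Either way it is collected after randomisation.
- **Study design.** The control group "will not be granted access to MT4C-In Care until the study period is over".
- **Intervention.** "Participants will access the MT4C-In Care tool as frequently as desired, and will choose which content to engage with", and "They may choose not to access MT4C-In Care at any time".

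The article does not say what value of use a control participant takes, or how self-selection into heavier use is to be handled.

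**The concern.** Level of use is not a baseline covariate. It is a behaviour that follows randomisation, is chosen by the participant, and has a meaningful value in one arm only. Carers with more hope, time or energy may use the site more and may also have better MCS scores whatever the site does. Adjusting the group comparison for such a variable does not give a dose effect, and it does not test the robustness of the intent-to-treat result, which is what a sensitivity analysis is normally for.

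What is at stake is interpretation. A significant use coefficient invites the conclusion that more use brings more benefit, even if the tool does nothing. In one extended form of the model, a real benefit could also appear to vanish once use is adjusted for. The article refers to outcomes in the plural and analyses five secondary outcomes in the same way, so the opportunity for misreading recurs.

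**Working it through.** The article gives no figure for this analysis, so there is none to reproduce. The check is algebra followed by simulation.

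**Inputs from the article:** 140 per arm; three visits; within-subject correlation 0.50; GEE with group, time and group x time; use recorded in the intervention arm only.

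**Assumed inputs:** a carer trait U (standard normal) raises MCS by b = 0.3 SD; use in the intervention arm is exp(0.8 + 0.5U + 0.5e), rounded, with e standard normal; data are complete.

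**1. Design matrix.** Let g be group (0/1) and D the amount of use, so the covariate is use = gD.
- *Controls coded 0.* Intercept, g and use have rank 3 of 3. Effect modification needs g x use, but g x gD = gD = use. Adding it gives rank 3 of 4. The use slope is therefore only the comparison of heavy with light users inside the intervention arm.
- *Controls left missing.* Complete cases all have g = 1, so g equals the intercept: rank 2 of 3, and the group effect is not estimable.

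**2. Plain covariate in the planned GEE, controls coded 0.** Use is constant over visits within a person. Group x time is a within-person contrast, so with complete balanced data it is the same with or without use (difference 0.000 in simulation).

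**3. Use x time added,** which the stated aim would seem to need. If U affects change in MCS, the within-arm slope of change on use is b x cov(U, use)/var(use). Ignoring rounding:
- mean use = exp(0.8 + 0.25) = 2.858
- var(use) = 2.858² x (exp(0.5) - 1) = 8.166 x 0.6487 = 5.298
- cov(U, use) = 0.5 x 2.858 = 1.429
- slope = 0.3 x 1.429/5.298 = 0.081 SD per unit of use
- bias in group x time = -0.081 x 2.858 = -0.23 SD, so a true 0.30 becomes 0.30 - 0.23 = 0.07

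With b = 0.2 the bias is -0.23 x 0.2/0.3 = -0.15 SD. With b = 0 it is zero.

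**4. Simulation of the GEE** (several hundred trials per scenario, b = 0.3, controls coded 0):

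| Model | Trait acts on | Group x time, true effect 0 | Group x time, true effect 0.30 | Use coefficient significant, true effect 0 |
|---|---|---|---|---|
| Use as plain covariate | level | about 0 (5.0% rejected) | 0.30 | use: about 72%, up to 79% in repeat runs |
| Use as plain covariate | change | about 0 | 0.30 | use: about 46% |
| Use and use x time | level | 0.01 (5.0% rejected) | 0.32 | use main effect, as in the first row |
| Use and use x time | change | -0.21 to -0.25 (about 32% rejected) | 0.06 to 0.07 | use x time: about 57% |

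**5. No confounding, benefit wholly through use.** In a model of change in MCS (assumed SD 10), a true 3-point effect acting only through use gives an adjusted group estimate of 0.0. The adjusted term is then the contrast at zero use, not the effect of offering the tool.

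**The case against.** The strongest defence has four parts.

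*The analysis is subordinate.* The article says "While outcome analysis will follow the intent to treat principle", and the use analysis is only exploratory. This stands, and it limits the seriousness of the point.

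*The literal model does not harm the treatment estimate.* This also stands. A reader might infer that the planned adjustment would bias the treatment effect or turn a real benefit into none. The article does not support that: with use as a plain covariate and complete data, group x time is unchanged. A figure such as -0.24 SD for the group coefficient comes from a single-follow-up regression on group and use. In the planned GEE with categorical time, the group term is the baseline difference, and group x time carries the hypothesis. Distortion of group x time needs more than the article states, such as use x time with a trait that predicts change. What survives is that the literal model does not answer its own question and still produces a misleading use coefficient.

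*Non-estimability is speculative.* A reader might infer that every control would drop out of the model. That follows only if use is left missing for controls. The coding is not stated, and zero is the natural value for people without access. It is a possibility to exclude, not a defect shown.

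*A complier effect answers a different question.* Correct: it gives the effect among users and says nothing about amount. It should therefore be paired with a descriptive analysis of amount and not presented as a dose-response.

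**Conclusion.** The point holds in a limited form. The article commits to a covariate that is self-selected, post-randomisation and confined to one arm, and the resulting model cannot show whether amount of use influences the intervention's impact. This lies in the choice of analysis, not in detail left to another document.

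The algebraic result (group x use identical to use when controls are zero) needs no assumption beyond that coding. The sizes do: 46 to 72% spurious significance for a use coefficient, and about -0.2 SD bias when use x time is added and the trait drives change, rest on an assumed 0.3 SD trait effect and an assumed distribution of use. A weaker trait gives smaller figures, and a trait that lowers MCS while raising use would reverse the sign. The intent-to-treat conclusion for MCS is not touched. The change is worth making before analysis, but the trial's main result does not depend on it.

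**What to change.** Replace the use-adjusted model with two clearly separated analyses.

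1. **Complier-average effect.** Define a user as anyone with any access in the 2 months. Use randomised group as the instrument and baseline MCS as a covariate, for example by two-stage least squares. Controls have no access, so non-compliance is one-sided. State the exclusion restriction: assignment has no effect in people who never access the site. Both arms receive the same educational document, which helps its plausibility. A threshold above any access would strain it, because lighter users might still benefit. State how use is handled for participants who miss the 2-month interview. Report the result beside the intent-to-treat effect.
2. **Amount of use.** Report use-outcome associations within the intervention arm only, adjusted for baseline, and label them non-randomised and descriptive.

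The cost is a little extra analysis of data already planned. Without covariates the complier effect is the intent-to-treat effect divided by the proportion of users, so its confidence interval is wider. It does not estimate a dose-response; under this design that question can be described but not settled by randomisation.
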